## Methods/Design

### Sample size and power

This is a novel piece of research examining how IPS works and develops within a criminal justice setting by means of a Realistic Evaluation (RE). It will yield valuable information for future studies, including the rates of recruitment and retention of participants, as well as the variation in the outcome measures, which is needed to undertake sample size calculations. The current sample size has been determined by the time and resources available: 20 (IPS) and 20 (No IPS) will have a power value of .60 and a critical z score = 1.645 [40] 1.

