### Offender interviews

Previous research indicates that the employment rate of offenders released from prison is 25 % [9]. The IPS literature consistently demonstrates that participation in IPS doubles the percentage of people in paid employment [41]. However, this excludes offenders who, for reasons cited earlier, face additional obstacles to employment. Therefore, in consideration of previous IPS research and the experience of the research team, an estimated hypothesis for the primary outcome is that 40 % of those on IPS will work at least one day in paid employment compared with 25 % for those who do not take part in IPS: at least eight of the intervention group of 20 will obtain work, as compared to five of the control group. A 15 % net increase in the competitive employment rate is both clinically and socially meaningful as not only would this reduce the range of costs to society that are associated with this population, but according to previous findings employment can have a positive impact on each individual’s life satisfaction and their mental health, especially if this is sustained [37, 38].

As there is no randomisation with regards to who takes part in IPS and who does not take part in IPS, motivation to gain employment will be measured, making it possible to control for the effect of differences in motivation on outcomes using logistic regression.

Given that the majority of recruitment and consent will be taken within prison the research team estimate that most (80 %) of those approached to participate in the research will take part. Furthermore, as not everyone who is approached will take part in the research, even though they may take part in IPS, it is believed that 36 people within each group will need to be approached.

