### Data collection

#### Validated measures

All of the measures seen in Table 1 are highly validated and will assess the mental health, social stability, including social network, and the motivation of each participant. Each measure is self-administered, however, the researcher will help each participant where necessary. The TAG is already routinely present on each client’s file and will be completed twice by staff who know the participant well. Each set of questionnaires will take around 30 minutes to complete.

**Table 1 Tab1:** Data collection measures and time frame for offender participants

*Measure*	*Baseline*	*6 months*	*12 months*
Threshold Assessment Grid (TAG) [42]		*√*	*√*
General Health Questionnaire-12 (GHQ-12) [43, 44]	*√*	*√*	*√*
Brief Symptom Inventory-18 (BSI-18) [45, 46]	*√*	*√*	*√*
Manchester Short Assessment of Quality of Life (MANSA) [47]	*√*	*√*	*√*
Social Network Analysis (SNA) [48]	*√*		*√*
Motivation and Readiness to Work scale (MTW) [49]	*√*	*√*	*√*
Reconviction Analysis			
Semi-structured Interview	*√*	*√*	*√*

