### Quantitative data

To determine whether there was a significant difference between those who took part in IPS and those who did not, concerning whether competitive employment was gained, a Chi-square analysis will be carried out at the six and 12 month intervals. Similarly, a logistic regression will also be carried out at these intervals in order to control for a participants’ motivation to work and assess covariates (e.g. age, gender, criminality) between both groups. Motivation to work will be controlled for during all comparisons, as the decision to seek employment is a personal choice.

Questionnaires pre and post IPS will be analysed using statistical independent sample t­tests, using a Statistical Package for the Social Science (SPSS) software, to determine whether overall significant improvements exist within mental health and social stability between those who did, and those who did not take part in IPS. A case by case examination of client yes/no responses in interviews, social stability measures (job contract and income, accommodation, social network etc.), and structured aspects within social stability questionnaires will be examined in conjunction with all other data, such as themes gained from interviews, to supplement all research questions and to make improvements and recommendations concerning IPS. Unemployment rates, jobs created data, fidelity to the IPS model and any changes in crime rates for particular areas will also be taken into account when examining results.

Descriptive data will be produced to meet the additional secondary outcomes; employment outcomes achieved. All other structured information from the relevant validated measures will be examined case by case for patterns of change amongst those who were part of IPS in comparison with those who were not part of IPS. Appropriate statistical analyses will account for any attrition variation between the IPS and no IPS control condition across the three data collection points. Missing data will also be excluded using the appropriate statistical techniques.

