## Discussion

The study will be carried out across a wide geographical area. A total of eight sites, seven prisons and one probation area are eligible to provide referrals to the study, including both people who do and do not want help to find competitive employment via the IPS service. This will therefore involve conducting research within the demands of a criminal justice setting, with a population many of whom have chaotic lifestyles.

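### The t-tests named for mental health and social stability cannot deliver the motivation adjustment that the plan promises for all comparisons, and the score to be tested is not stated

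*Protocol article*

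**What the plan says.** All references are to the protocol article.

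- **Quantitative data, first paragraph.** Employment is compared by chi-square and also by logistic regression, at 6 and 12 months, the regression being there to control for motivation. The paragraph ends with a general commitment: "Motivation to work will be controlled for during all comparisons, as the decision to seek employment is a personal choice".
- **Quantitative data, second paragraph.** "Questionnaires pre and post IPS will be analysed using statistical independent sample" t-tests, in order "to determine whether overall significant improvements exist within mental health and social stability between those who did, and those who did not take part in" the intervention. It does not say whether the tested variable is the follow-up score or the change from baseline.
- **Offender interviews.** "As there is no randomisation with regards to who takes part in IPS and who does not take part in IPS", motivation will be measured, "making it possible to control for the effect of differences in motivation on outcomes using logistic regression".
- **Discussion.** The sites refer participants "including both people who do and do not want help to find competitive employment via the IPS service".
- **Table 1.** GHQ-12, BSI-18, MANSA and MTW are scheduled at baseline, 6 and 12 months, and the Social Network Analysis (SNA) at baseline and 12 months. TAG is ticked at 6 and 12 months only. The text under Validated measures says TAG is already routinely on file "and will be completed twice by staff who know the participant well".

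**The concern.** The general commitment and the named test cannot both be carried out. The only adjusted models in the article are logistic regressions, for employment and for the propensity-matched reoffending comparison. No model named for the continuous questionnaires can take a covariate.

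This matters because participants are not randomised, and willingness to seek work is part of what separates the groups. A difference in motivation is therefore expected, and a difference in baseline mental health is plausible. If either is related to later scores, an unadjusted comparison partly measures who chose IPS rather than what IPS did. Leaving the tested score open adds to this, because the follow-up and change-score versions are biased under different conditions and could give different answers from the same data.

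**Working it through.** **The plan's own figure.** No power is stated for the questionnaires. The only power statement is "20 (IPS) and 20 (No IPS) will have a power value of .60 and a critical z score = 1.645", with no effect size beside it. Taking the primary-outcome rates of 40% and 25%, a one-sided pooled test gives about 0.26, not 0.60. The footnote marked there is not shown and may hold other inputs. That is a separate matter and nothing below rests on it.

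**Inputs.** From the article: 20 per group, so √(n/2) = √10 = 3.162. Assumed, because the article gives none of them: two-sided 5% test, within-group SD 1, pre-post correlation ρ = 0.6 (range 0.5 to 0.7), and the imbalances stated below.

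**Formulas.** With group difference d in the tested score:
- follow-up t-test: noncentrality 3.162·d, 38 df
- change-score t-test: 3.162·d/√(2(1−ρ)), and √0.8 = 0.894 at ρ = 0.6
- ANCOVA on baseline: d/√[(1−ρ²)(2/n + D²/38)], 37 df, where D is the baseline imbalance and √(1−0.36) = 0.8

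**1. Motivation differs, no IPS effect.** MTW imbalance 0.8 SD, coefficient 0.3, baseline scores balanced: spurious difference 0.8 × 0.3 = 0.24.
- follow-up: 3.162 × 0.24 = 0.759, rejection 11.5%
- change: 0.759/0.894 = 0.849, rejection 13%
- ANCOVA on baseline only: 0.759/0.8 = 0.949, rejection 15%
- ANCOVA on baseline and MTW: about 5% (simulated)

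Only the last model keeps the promise. Adjusting for baseline alone does not.

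**2. Baseline health differs by 0.5 SD, no IPS effect, same regression line in both groups.**
- follow-up: d = 0.6 × 0.5 = 0.30; 0.949; rejection 15%
- change: d = 0.30 − 0.50 = −0.20; 0.20 × 3.162/0.894 = 0.707; rejection 11%
- ANCOVA: d = 0; rejection 5%

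Over ρ = 0.5 to 0.7 the follow-up test rejects in 12% to 19% of studies, and the change-score test in 12% falling to 9%.

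**3. The same 0.5 SD gap, but stable at both times.** Now the change score has d = 0 and holds 5%. ANCOVA keeps a bias of (1 − 0.6) × 0.5 = 0.20 SD. Its standard error is √[0.64 × (0.1 + 0.25/38)] = 0.261, so the noncentrality is 0.766 and it rejects in 12%. At ρ = 0.5 and 0.7 the bias is 0.25 and 0.15 SD.

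**4. Power for a true 0.6 SD effect, balanced groups.**
- follow-up: 1.897, 46%
- change: 1.897/0.894 = 2.121, 54%
- ANCOVA on baseline: 1.897/0.8 = 2.372, 64% by formula and 62% simulated, since chance imbalance costs a little

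**5. The price of adding MTW.** In scenario 4, with MTW unrelated to outcome and imbalanced by 0.5, 1.0 or 1.5 SD, simulated power is about 59%, 53% and 43%.

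**6. What adjustment leaves behind.** In a null simulation with a 0.5 SD baseline gap, a coefficient of 0.8 on the true baseline and baseline reliability 0.8, the mean estimates are 0.40 (follow-up), −0.09 (change) and 0.09 (ANCOVA). Adding an unmeasured confounder (0.5 SD gap, coefficient 0.3) gives 0.54, 0.05 and 0.23.

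**The case against.** Several stronger readings are tempting, and the document does not support them.

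- **That the plan cannot use the baseline score.** The pre-and-post wording, with improvement as the aim, allows a t-test on change scores, which does use it. What stands is that the score is unspecified, and that neither version adjusts for motivation.
- **That ANCOVA would remove the bias.** Without randomisation it would not. Step 3 shows a plausible case in which the change score is unbiased and ANCOVA is not, and step 6 shows residual bias from measurement error and unmeasured confounding. Neither method dominates in self-selected groups.
- **That ANCOVA adds power at no cost.** The gain depends on an unstated pre-post correlation. Step 5 shows that a 1 SD imbalance in MTW brings power slightly below the change-score test, and 1.5 SD brings it below the follow-up test as well.
- **That the chi-square breaks the same promise.** It does not, because a motivation-adjusted logistic regression accompanies it at the same time points.
- **That TAG can show no change from before IPS.** As scheduled it has no baseline, but a value is said to be on file. Its date is not given, so this is open.

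It can also be said that these are secondary outcomes in a small, resource-limited realistic evaluation, that the questionnaires are read case by case alongside interviews, and that an article may leave model detail to a fuller document. The first two points lower the severity and are accepted. The third covers the unspecified score at most: the article names a particular test and makes a commitment that the test cannot meet, which is a conflict within the text and not an omission.

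**Conclusion.** The point holds as a should-fix. The t-tests named for mental health and social stability cannot control for motivation, contrary to the plan's own statement, and the score to be tested is not fixed. With self-selected groups, differences in motivation and baseline health can be attributed to IPS. Under the assumptions shown, the false-positive rate of a nominal 5% test rises to roughly 9% to 19%, depending on the score tested and the source of imbalance. These sizes are illustrative: the article gives no correlation, imbalance or motivation effect. The contradiction itself needs no assumption. The primary employment analysis is unaffected.

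**What to change.** 1. Replace the t-tests by a linear model of each follow-up score on group, the baseline value of the same scale and baseline MTW. Use ANCOVA, or a mixed model over 6 and 12 months for GHQ-12, BSI-18 and MANSA. SNA has only the 12-month follow-up. State the Table 1 time points in place of the pre-and-post wording.
2. Keep the unadjusted comparison as descriptive.
3. Report a change-score model, also adjusted for baseline MTW, as a sensitivity analysis, since step 3 shows that either form may be the less biased one.
4. Say in the text that adjustment reduces confounding by the measured variables and does not remove it.
5. For TAG, check whether the value on file predates IPS. If it does, record it as baseline and adjust for it. If not, report TAG without any claim of change from before IPS.

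**Cost.** For the scales with a baseline this is a change of analysis wording, as the data are already scheduled. It uses two degrees of freedom per model (36 instead of 38 with 40 participants analysed at one time point), and some precision is lost if the groups differ strongly on MTW or baseline. Recording a baseline TAG is a small change to data collection.

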**Methods/Design:**

A Realistic Evaluation (RE) design will address the questions “What works, for whom, and in what circumstances?” This study includes pre and post comparisons for a cohort of approximately 20 people taking part in IPS, and a similar number of controls, over a one year period. The RE also consists of interviews with practitioners and offenders in order to understand how IPS works and develops within the criminal justice system (CJS). By applying this framework the research can go from discovering whether IPS works, to how and why (or why not) IPS works. This is achieved by examining where the intervention is occurring (Context (C)), the mechanisms (M) that create particular behaviours, and how the outcomes (O) from the intervention all come together (CMOs). Employment outcomes will also be examined for all participants.

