### Primary and secondary outcome measures

The primary outcome measure for the study is:

Employment gained in a competitive market through the IPS intervention (yes/no).

The secondary outcome measures for the study are:

Mental health, motivation to work, social stability, admissions to a psychiatric hospital, and offending behaviour

This will be assessed at 6 and 12 month intervals. The following information will also be collected where relevant:Time (days) until first competitive employmentJob tenure of competitive employment (hours/days/weeks/months worked from start of IPS)Job stability (working hours/contract gained)Income from employment

Leaving the study for any reason will be measured to assess any bias in the results.

Participant medical records­ hospitalisations, and the reasons for these, will be sought to fully understand the primary and secondary outcomes. Previous hospitalisations predict and increase the chance of future hospitalisation [39] and therefore may interrupt employment or the potential to gain employment during the study.

This medical information will also be very important when examining the mental health and motivation to work of participants throughout the study. By understanding if the participant has had any very recent previous and current hospitalisations, and why, the researcher can control for how this may mediate time until employment, participant dropouts, job tenure, and hours worked.

Information will also be sought from the participants’ prison records. Prison records would reveal any history of offending, index offence information, and the duration of sentence/community order. This information will also be important when examining any barriers a participant may have had when seeking competitive employment.

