#### Semi-structured interviews

Semi-structured interviews will last between 30 to 60 minutes, a total of less than 90 minutes per offender. The researcher will follow a topic guide (available from the authors on request). It is also important to note that participants may be recalled to prison for a number of reasons other than reoffending, therefore, this will be taken into account and questions and/or prompts within this topic guide will be asked as appropriate.

Interviews will be carried out to gain an understanding of the individuals’ motivations and expectations of the IPS service and to understand how the intervention is working. Interviews will also generate data concerning the impact of IPS and/or any employment gained on the core areas under investigation- mental health, social stability, and recidivism.

All participants will initially be asked questions about their offending behaviour. Participants who have reoffended will be given an opportunity to discuss their offending behaviour and the reasons for it, within the semi-structured interviews. Those who do not reoffend will be asked questions about what they believe has helped them to desist from criminal behaviour.

The initial and subsequent interviews will take place in prison and then in the community, respectively, however, this may vary depending on referral and participant location at time of interview.

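### Excluding missing data puts the employment comparison at risk of bias in an unknown direction, and the plan does not reconcile it with its promise to account for attrition

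*Protocol article*

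**What the plan says.** The rule stands in the protocol article, Quantitative data: "Missing data will also be excluded using the appropriate statistical techniques". The sentence before it reads: "Appropriate statistical analyses will account for any attrition variation between the IPS and no IPS control condition across the three data collection points". Neither names a technique.

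For the primary outcome (competitive employment, yes/no), "a Chi-square analysis will be carried out at the six and 12 month intervals", with a logistic regression alongside. Questionnaires are compared by independent-sample t-tests.

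Other sections bear on who will be missing:

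- Primary and secondary outcome measures: "Leaving the study for any reason will be measured to assess any bias in the results". On recent hospitalisation, the same section says that "the researcher can control for how this may mediate time until employment, participant dropouts, job tenure, and hours worked", having noted that hospital stays may interrupt work or the chance of it.
- Discussion: the research will be done "with a population many of whom have chaotic lifestyles".
- Semi-structured interviews: "participants may be recalled to prison for a number of reasons other than reoffending". The topic guide is to allow for this.
- Abstract, Methods/Design: "Employment outcomes will also be examined for all participants". No analysis set is defined.

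**The concern.** A chi-square test or a t-test needs an outcome for each person counted. Excluding missing data therefore in practice means analysing only those whose outcome was obtained. That is harmless if loss is unrelated to employment. The article gives reason to doubt this: it names hospitalisation as something that may affect both dropout and employment.

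The damaging case is outcome-related loss that differs between the groups. It is plausible here because the groups are not randomised and only the IPS group has an employment specialist, but the article neither states it nor gives its direction. With 20 per group, each excluded person is 5% of an arm. What is at stake is whether the reported difference reflects IPS or who could still be reached.

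**Working it through.** **Inputs from the article.** Offender interviews: 8 of 20 on IPS and 5 of 20 controls are expected to work. This reproduces as 8/20 = 40%, 5/20 = 25%, difference 15 points, odds ratio (0.40/0.60)/(0.25/0.75) = 2.00.

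**Inputs assumed.** No dropout rate is given; Sample size and power lists retention among the things to be learned. The retention figures below are chosen to show the range.

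**Formula.** Let p be the true employment rate, rE the proportion of employed participants retained and rN the proportion of non-employed participants retained.

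- Complete-case rate = p·rE / [p·rE + (1 − p)·rN].
- Complete-case odds ratio = true odds ratio × (rE/rN in IPS) / (rE/rN in control).
- Rate with missing counted as not employed = p·rE.

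Example, row d, IPS: 0.40 × 0.90 / (0.40 × 0.90 + 0.60 × 0.60) = 0.36/0.72 = 50.0%.

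| Pattern of loss | IPS rE / rN | Control rE / rN | Complete-case rates | Difference (points) | Odds ratio | Difference, missing as not employed |
|---|---|---|---|---|---|---|
| a. Unrelated to employment | .70 / .70 | .70 / .70 | 40.0% v 25.0% | 15.0 | 2.00 | 28.0 − 17.5 = 10.5 |
| b. Differs by group only | .90 / .90 | .60 / .60 | 40.0% v 25.0% | 15.0 | 2.00 | 36.0 − 15.0 = 21.0 |
| c. Outcome-related, same in both | .90 / .60 | .90 / .60 | 50.0% v 33.3% | 16.7 | 2.00 | 36.0 − 22.5 = 13.5 |
| d. Outcome-related, IPS only | .90 / .60 | .75 / .75 | 50.0% v 25.0% | 25.0 | 3.00 | 36.0 − 18.75 = 17.25 |
| e. Outcome-related, control only | .75 / .75 | .90 / .60 | 40.0% v 33.3% | 6.7 | 1.33 | 30.0 − 22.5 = 7.5 |
| f. Outcome-related, stronger in control | .90 / .80 | .90 / .50 | 42.9% v 37.5% | 5.4 | 1.25 | 36.0 − 22.5 = 13.5 |
| g. Outcome-related, stronger in IPS | 1.00 / .60 | 1.00 / .80 | 52.6% v 29.4% | 23.2 | 2.67 | 40.0 − 25.0 = 15.0 |

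If IPS had no effect (25% in both groups), pattern d would give 0.225/0.675 = 33.3% v 25.0%, a spurious 8.3 points.

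Rows a to c mark the limits of the concern: the odds ratio moves only when rE/rN differs between groups. The last column shows that counting missing as not employed is not neutral either. In row b it creates a bias that exclusion does not have.

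**Bounds.** Suppose a fraction f is missing in each group and the observed rates are 40% and 25%. The difference with missing as not employed is 0.15(1 − f), and the worst and best cases are 0.15(1 − f) − f and 0.15(1 − f) + f.

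| f | Missing as not employed (points) | Worst to best case (points) |
|---|---|---|
| 10% | 13.5 | +3.5 to +23.5 |
| 20% | 12.0 | −8.0 to +32.0 |
| 30% | 10.5 | −19.5 to +40.5 |
| 40% | 9.0 | −31.0 to +49.0 |

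Loss near 30% is not far-fetched. Approaching 36 per group with 80% uptake gives 28.8 entrants. If the target of 20 means completers, the implied loss is 1 − 20/28.8 = 31%. That is an inference; the article does not say so.

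**The case against.** **No bias has been shown.** A reader might infer that the complete-case rates are biased, or that unequal dropout alone would bias them. The documents support neither. They give no dropout rate and no direction, row b shows that unequal dropout by itself leaves the rates intact, and row c leaves the odds ratio, which the logistic regression estimates, at 2.00. This stands: the point is a risk, not an established error.

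**Recall to prison is not stated as a cause of loss.** It is tempting to treat people back in custody as unreachable. Semi-structured interviews plans for recalled and reoffending participants and lets the interview setting vary; Discussion lists seven prisons among the sites; Ethics and consent offers payment throughout. This also stands, so the concern rests on hospitalisation and unstable lives.

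**Exclusion and attrition adjustment can coexist.** One might say that exclusion throws away what an adjustment needs. It does not: leavers' baseline motivation, GHQ-12, BSI-18 and MANSA remain and could support weighting or a comparison of leavers with stayers. But the article does not say that this is how the two sentences fit together.

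**The wording is loose and the article is condensed.** It says data, not participants, and the choice of technique may be left to a fuller document. The missing name of a technique is therefore not the finding. The finding is that the one rule stated is exclusion, placed beside tests in which a missing outcome drops the person.

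**The shifts are small beside the noise.** The standard error of the difference at 20 per group is √(0.24/20 + 0.1875/20) = 14.6 points, larger than the shift in any complete-case row. True, but bias adds to sampling error, and a confidence interval computed on completers does not show it.

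**Conclusion.** The concern holds as a risk. Exclusion is the stated rule, the article's own account of hospitalisation makes loss unrelated to employment doubtful, and the rule is not reconciled with the promise to account for attrition. If outcome-related loss differs between groups, a true 15-point difference could appear as about 5 to 25 points (5.4 in row f, 25.0 in row d). These figures rest on the article's 40% v 25% and on assumed retention. They illustrate and do not bound the error; its actual size and direction cannot be known from the article. The rule should be changed before the data are analysed.

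**What to change.** **Primary outcome.** Replace the exclusion sentence with three rules.

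1. All enrolled participants stay in the denominator of their group.
2. Where follow-up is missing, status is completed as far as possible from the medical, prison and PNC records already sought, by the same procedure in both groups. Confirm that the look-up reaches the enrolled no-IPS participants. IPS service records should not be used for this: they exist for one group only, and they are not among the records or the consent that the article names. Records of custody or admission can make a new job in that period unlikely, but they do not show work before it, so some participants will remain unknown.
3. For those still unknown, report missing-as-not-employed and best-case/worst-case analyses beside the complete-case result. None of these is right on its own, as row b shows.

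**Questionnaires.** For GHQ-12, BSI-18 and MANSA, which Table 1 schedules at baseline, 6 and 12 months, use a mixed model on all available scores, adjusted for baseline motivation, instead of t-tests on those with complete data. This also delivers the adjustment for motivation that the article promises for every comparison and that a t-test cannot provide. The model still assumes that missingness depends on observed data. TAG (no baseline) and SNA (no 6-month score) have two time points each and are analysed on the scores available.

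**Cost.** A little more analysis and record look-up, and a wider stated uncertainty. No added visits are needed.

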### Recruitment

This research was initially designed for delivery in Her Majesty’s Prison Service (HMPS) across three prisons. However, in order to maximise referrals onto IPS and the current study participants will be recruited from a total of seven prisons and from offenders serving community orders. Community referrals onto IPS will be taken via Integrated Offender Management (IOM). The IOM is part of a multidisciplinary team that looks after ex­offenders in the community and includes, for example, the National Probation Service (NPS), Police, and Drug and Alcohol Teams.

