### Reconviction analysis

A sample of similar size matched on criteria that influence reoffending, will be compared with the study participants to determine the probability of reconviction with and without IPS involvement. This ‘reconviction analysis’ will also involve comparisons between the two groups on new index offence, sentence length, and overall circumstances.

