By examining Police National Computer (PNC) data the proven one year re­offending rates of individuals who took part in IPS will be made clear. Specifically, whether any offence has been committed and whereby a conviction, caution, warning or reprimand was received within the one year follow up and six month waiting period [56]. This will also give an indication of the severity and regularity of reoffending in comparison to each individual’s own previous offending behaviour.

To generate stronger findings that go beyond whether an individual offends or not and how this compares to their previous offence history it is important to determine what would have happened to the participants on IPS should they not have taken part, an estimate is needed. This estimate is known as the ‘counterfactual’ [57] and will enable a comparison in reoffending rates of those who took part in IPS with those who did not. Making this comparison ensures that the only major difference in characteristics between both groups is the IPS intervention. In order to isolate the effects of IPS in this way those on IPS will be matched on key factors which influence reoffending with a comparator group (No IPS). A logistic regression, Propensity Scored Matching (PSM), will be utilised to carry out this comparison.

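### Comparing IPS participants' reoffending with their own earlier offending can show a change with no IPS effect; only the difference from the matched No IPS group should be interpreted

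*Protocol article*

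**What the plan says.** The Protocol article, under Quantitative data, takes reoffending from police records: "By examining Police National Computer (PNC) data the proven one year re­offending rates of individuals who took part in IPS will be made clear". Convictions and cautions count, as do warnings and reprimands, if they fall "within the one year follow up and six month waiting period". The comparison at issue follows: "This will also give an indication of the severity and regularity of reoffending in comparison to each individual’s own previous offending behaviour". Coming directly after a sentence about people who took part in IPS, it reads as a comparison within that group.

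The article gives no length for the earlier period. Under Primary and secondary outcome measures it says of a different source: "Prison records would reveal any history of offending, index offence information, and the duration of sentence/community order". On who enters the study, the Recruitment section says that "participants will be recruited from a total of seven prisons and from offenders serving community orders".

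The next paragraph of Quantitative data says that stronger findings need more than a comparison with a person's own history, because "it is important to determine what would have happened to the participants on IPS should they not have taken part". It plans a No IPS group matched by propensity score. The Reconviction analysis section agrees: "A sample of similar size matched on criteria that influence reoffending, will be compared with the study participants". The outcomes listed there are the probability of reconviction and then new index offence, sentence length and overall circumstances.

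**The concern.** The two periods being compared are not alike. The later one is a fixed follow-up in which a person may or may not offend. The earlier one belongs to people who are in the study because they offended, so it holds at least the index offence. That offence was serious enough for custody or a community order, whereas the follow-up also counts cautions, warnings and reprimands. Severity and regularity before IPS are thus raised by selection, and regression to the mean can look like improvement.

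Research question 5 asks for the effect of IPS on reoffending. With about 20 people on IPS, a striking before-after change could be quoted alongside, or instead of, an imprecise matched estimate. For regularity the risk is greater, because the own-history sentence is the only place where the article names that outcome.

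**Working it through.** The article gives no offending rate, so there is no figure of its own to reproduce. The check asks what the own-history comparison shows if IPS has no effect.

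**Inputs**
- Follow-up: one year (Quantitative data). I take offences as counted over that year.
- Earlier period: L years, not stated, varied from 1 to 10.
- Every person has an index offence (Recruitment; Principal inclusion criteria).
- Rate λ of proven offences per person-year, the same before and after: assumed, mainly 0.3 to 1.0.

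**1. Constant rate, look-back ending with the index offence, index offence counted.** Annual rate before = (1 + λL)/L; after = λ; relative fall = 1/(1 + λL).
- L = 1, λ = 0.3: 1.3 to 0.3, a fall of 1/1.3 = 77%.
- L = 1, λ = 0.5: 1.5 to 0.5, a fall of 1/1.5 = 67%.
- L = 1, λ = 1.0: 2.0 to 1.0, a fall of 1/2 = 50%.
- L = 5, λ = 0.5: 0.7 to 0.5, a fall of 1/3.5 = 29%.
- L = 10, λ = 1.0: 1.1 to 1.0, a fall of 1/11 = 9%.

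The share with any offence is 100% before, by selection, and 1 − exp(−λ) in the year after: 26%, 39% and 63% at λ = 0.3, 0.5 and 1.0.

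**2. Rates that differ between people.** Let rates follow a gamma distribution with mean m and shape k, and select people with at least one offence in the earlier L years. With q = k/(k + mL), the annual rate before = m/(1 − q^k), and after = m(1 − q^(k+1))/(1 − q^k).
- L = 1, m = 0.5, k = 0.5: 1.71 to 1.10, a fall of 35%.
- L = 1, m = 0.5, k = 1: q = 0.667; 0.5/0.333 = 1.50 to 0.5 × 0.556/0.333 = 0.83, a fall of 44%.
- L = 1, m = 1, k = 1: 2.0 to 1.5, a fall of 25%.
- L = 1, m = 2, k = 1: 3.0 to 2.67, a fall of 11%. The artefact shrinks at high rates.
- L = 5, m = 0.5, k = 1: q = 0.286; 0.5/0.714 = 0.70 to 0.5 × 0.918/0.714 = 0.64, a fall of about 8%.

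**3. Custody time ignored.** If a share f of the earlier period was spent in custody and calendar time is used, the rate before = (1 + λL(1 − f))/L.
- λ = 1, L = 5, f = 0.25: (1 + 3.75)/5 = 0.95 before, 1.0 after.
- λ = 1, L = 5, f = 0.5: (1 + 2.5)/5 = 0.70 before, 1.0 after: an apparent rise.

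**4. After the fix.** With the index offence excluded and time at liberty as denominator, a constant rate gives λ before and λ after, so the expected change is zero. Any artefact left because real rates vary is common to a No IPS group selected and handled in the same way. The between-group difference in change then has expectation zero under no effect, provided the matching succeeds.

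**The case against.** The article does not rest its claim about reoffending on this comparison. It calls it an indication, attaches no test or estimate, says at once that stronger findings must go further, and plans a matched counterfactual. Comparing the groups on the follow-up year alone does not import the artefact. That stands: a reader might infer that a before-after fall is the planned evidence for research question 5, and the text does not support that.

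A reader might also infer that a fall must appear. Step 3 shows otherwise: direction and size depend on the look-back, the index offence and custody time. The one-year figures lie near the unfavourable end. Nor does the article say that the whole criminal history is used; the sentence on any history of offending concerns prison records and does not define the police-record look-back.

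Finally, a journal article may leave the look-back length to the full protocol, and its absence alone is no finding. That also stands, but it does not settle the matter. The choice the article does state is own history as comparator, for the IPS group, in people selected for having offended, and stating a look-back would not remove that bias. The matched analysis partly covers severity through new index offence and sentence length. It speaks of reoffending rates, but does not name how often people reoffend.

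**Conclusion.** The point holds as a limited one about a descriptive comparison. Setting IPS participants' severity and regularity of reoffending against their own past can show a change with no IPS effect. At assumed rates of 0.3 to 1.0 per person-year, a one-year look-back that includes the index offence gives a false fall of about 25% to 77%. With five years the fall is smaller (29% and 8% in the two five-year examples), and it can become a rise if custody time is ignored. These figures illustrate the count of offences; the severity argument is qualitative. They rest on assumed rates and on Poisson offending that does not change over time. The matched No IPS comparison remains the basis for research question 5, and nothing here shows it to be biased by this route. What is left is an uncontrolled comparison that invites over-reading, and an outcome, regularity, with no named comparator.

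**What to change.** Amend the reoffending paragraphs of Quantitative data as follows:
- Use a look-back of the same length as the follow-up, counted as time at liberty and excluding the index offence.
- Count earlier offences and grade their severity under the same proven-offence rule as in the follow-up.
- Compute the change in severity and regularity in both the IPS and the matched No IPS group, and name regularity among the matched outcomes.
- Interpret only the between-group difference, and state that the within-IPS change alone is not evidence of an IPS effect.

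The change is mostly one of wording, but it has two costs. Dated offence and custody records are needed for the matched group as well, and the article does not establish that these will be available. A before-after fall can also no longer be cited for IPS on its own. If the records cannot be had for the comparators, the last statement should still be added.
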